### Statistical methods {14}

The required sample size was calculated using the sample size calculation OpenEpi® software version 3.01 available online [24]. In testing the null hypothesis at a 95% level of confidence interval (CI), the error rate of 5% with power = 80%. We used the following formula for sample size calculation:
$$ \mathrm{n}1=\left(\mathrm{Z}\upalpha /2+\mathrm{Z}\upbeta \right)2\ast \left(\mathrm{p}1\left(1-\mathrm{p}1\right)+\mathrm{p}2\left(1-\mathrm{p}2\right)\right)/\mathrm{r}\left(\mathrm{p}1-\mathrm{p}2\right)2 $$

and

n2 = r*n1

where:

n1 = number of exposed (intervention group)

n2 = number of unexposed (control group)

Zα/2 = standard normal deviate for the two-tailed test based on alpha level (relates to the confidence interval level) [alpha = 0.05]

Zβ = standard normal deviate for the one-tailed test based on beta-level (relates to the power level) [beta = 0.2]

r = ratio of unexposed to exposed = 1

p1 = proportion of exposed with the outcome: incidence in intervention group: 34% (we used results from two studies that showed and an improvement between 34 and 69% after delivering the interventions to pregnant women) [18, 25].

p2 = proportion of unexposed with the outcome: incidence in the control group: 70% (since no similar studies have been conducted locally; hence, the estimate p1 was set to 70%).

The sample size needed for each group would be 29 pregnant women, and the total would be 58 participants.

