### Statistical methods

#### Statistical methods for primary and secondary outcomes {20a}

Quantitative variables will be described as mean and standard deviations, whereas the frequency with percentages will be calculated for categorical variables. Both the intervention group and control groups will be described in a table with all the characteristics. Chi-square test will be applied to compare percentages of categorical variables. Regression analysis will be carried to stratify data to eliminate potential confounders and effect modifiers. P value 0.05 (two-tailed) was considered for statically significant level.

We will analyze each continuous outcome with a linear mixed-effects regression model to account for the repeated measures over time. We will analyze binary outcomes with a logistic mixed-effects model. Mixed-effects models are the recommended statistical technique for analyzing clinical trials when outcomes are collected at repeated time points. This trial included outcome data at gestation weeks 14 to 40, 3 to 5 weeks postnatal, 2 to 4 months postpartum, 5 to 7 months, and 8 to 10 months postpartum or postnatal available for all participants who will be randomly assigned. The logistic mixed-effects model has the advantage of implicitly accounting for data missing at random. The estimated (adjusted) effect differences from these analyses therefore will be reported. The linear mixed-effects models will include the response variable, timepoint, randomized group, and baseline score as fixed effects. We will model an interaction between time and the randomized group as a fixed effect to estimate treatment effect at all timepoints. Gestational age and postpartum weeks will be included as covariates in the model. We will calculate standardized effect sizes with Cohen’s d.

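### The baseline score is named as a fixed effect for the linear mixed models only; the logistic mixed model for binary outcomes should name it too

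*Protocol article*

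**What the plan says.** Section {20a} of the protocol article assigns continuous outcomes to a linear mixed-effects model. For the rest it says "We will analyze binary outcomes with a logistic mixed-effects model". It then lists fixed effects for one of the two: "The linear mixed-effects models will include the response variable, timepoint, randomized group, and baseline score as fixed effects".

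The next two sentences add a time-by-group interaction, gestational age and postpartum weeks. Neither is restricted to the linear or the logistic model. No sentence gives the logistic model a baseline term, and none says that it is to have none.

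Three other places bear on the point:
- **Table 1** schedules the depression, anxiety and phobia assessments at T0 and at the later visits. Its footnote puts T0 in gestational weeks 14 to 27, after allocation, and the first intervention session at T1.
- **The sample size section {14}** compares two proportions: "p1 = proportion of exposed with the outcome: incidence in intervention group: 34" per cent, against "p2 = proportion of unexposed with the outcome: incidence in the control group: 70" per cent. It concludes: "The sample size needed for each group would be 29 pregnant women, and the total would be 58 participants".
- **The outcomes section {12}** defines the primary outcomes as scores on the three scales and changes in those scores.

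**The concern.** The section fixes the baseline term for one model and is silent for the other. Followed literally, the logistic model would receive group, time, their interaction, gestational age and postpartum weeks, but not the T0 score of the scale being analysed. That score is collected anyway, and the power statement in {14} concerns a binary comparison.

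Two things are at stake. First, if the T0 score predicts later status, leaving it out gives away precision in a trial of 58 women whose calculation has no allowance for dropout. Second, the continuous and binary analyses of the same scale would rest on different adjustments, so they could disagree for that reason alone.

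**Working it through.** **Inputs from the documents.** Intervention proportion p1 = 0.34, control proportion p2 = 0.70, "r = ratio of unexposed to exposed = 1", "the error rate of 5% with power = 80" per cent (all {14}); two-sided 0.05 ({20a}); 29 per arm ({14}).

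**Input not in the documents.** The correlation between the T0 score and the later outcome. It is assumed below and varied.

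**Step 1: the plan's own figure.**
- Formula as printed (unpooled): (1.960 + 0.842)² × (0.34×0.66 + 0.70×0.30) / 0.36² = 7.849 × 0.4344 / 0.1296 = 26.3, so 27 per arm.
- Pooled variance, mean proportion 0.52: [1.960 × √(2×0.52×0.48) + 0.842 × √0.4344]² / 0.1296 = (1.385 + 0.555)² / 0.1296 ≈ 29.0. Strict rounding up gives 30; power at 29 per arm is 79.96%.

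The stated 29 is reproduced within rounding by the pooled form. Power without a baseline term is therefore about 80%.

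**Step 2: approximate gain.** With r the within-arm correlation between T0 score and binary outcome, the standardised effect is divided by √(1 − r²):

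power = Φ(2.800 / √(1 − r²) − 1.960), where 2.800 = 0.840 + 1.960 corresponds to 79.96%.

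| r | Power |
|---|---|
| 0 | 80.0% |
| 0.2 | 81.5% |
| 0.3 | 83.5% |
| 0.4 | 86.3% |
| 0.5 | 89.9% |
| 0.6 | 93.8% |

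**Step 3: simulation.** 29 per arm, one visit, no dropout, 4,000 trials per setting. A latent normal outcome is correlated with the T0 score and cut to give 34% and 70%. Logistic regression is fitted without and with the T0 score.

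| Latent correlation | Resulting r | Likelihood-ratio test | Gain (points) | Wald test | Gain (points) |
|---|---|---|---|---|---|
| 0.3 | 0.23 | 79.7% to 82.9% | 3.2 | 79.7% to 81.7% | 2.0 |
| 0.4 | 0.30 | 80.3% to 85.2% | 4.9 | 80.3% to 83.7% | 3.5 |
| 0.5 | 0.38 | 80.9% to 87.5% | 6.6 | 80.8% to 86.0% | 5.2 |
| 0.6 | 0.46 | 80.6% to 90.4% | 9.8 | 80.6% to 89.0% | 8.4 |
| 0.7 | 0.53 | 79.8% to 92.9% | 13.1 | 79.7% to 91.5% | 11.8 |

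Separate runs of the same kind gave likelihood-ratio gains of 3 to 4 points at 0.3, 7 to 8 at 0.5 and 12 to 14 at 0.7. The simulation error of one power estimate is about √(0.8×0.2/4000) = 0.6 points.

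**Cross-check.** Putting r = 0.38 into step 2 gives Φ(2.800/0.925 − 1.960) = Φ(1.067) = 85.7%, a gain of 5.7 points, between the two tests' results at latent 0.5.

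**Step 4: type I error.** With the T0 score, 4.3% to 5.1% (Wald) and 5.1% to 5.9% (likelihood ratio; up to 6.5% in a separate run). Without it, about 4.4% to 4.7% (4.3% to 5.6% in a separate run). A small part of the likelihood-ratio gain reflects that slightly higher rejection rate: at correlation zero, power moves from 80.9% to 81.7%.

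**Step 5: other rates.** With the 34.4% pandemic depression prevalence from the Background as the control rate and an assumed 10% in the intervention arm, power goes from 65.1% to 70.5% at latent 0.5, a gain of 5.4 points.

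**The case against.** The strongest reply is that exclusion is being read out of silence. No list of terms is given for the logistic model, {20a} promises adjusted effect estimates, and {20c} leaves all analysis details to a statistical analysis plan that is not shown. This stands in part: a reader might infer that the plan deliberately drops the baseline score from the logistic model, and the text does not say that. What remains is that {20a} already fixes the term and attaches it to the linear models by name, while its neighbouring sentences on the interaction and on gestational age are general. An analysis plan that follows this wording would carry the asymmetry forward.

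Second, the primary outcomes in {12} are scores, with no binary version or cut-off defined there, and their model already includes baseline. This stands. A reader might infer that the primary analysis loses power; the documents do not support that.

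Third, a reader might take a single figure, such as 7 points, as the loss in this trial. It is not one. It follows only from an assumed latent correlation near 0.5, one visit and a likelihood-ratio test, and no test is specified.

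Fourth, a reader might take the chi-square test in {20a} as the planned unadjusted comparison of outcomes. It directly follows the sentence on tabulating group characteristics and reads as descriptive; binary outcomes are assigned to the logistic mixed model.

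Fifth, chance imbalance at baseline is not bias in a randomised comparison, and the unadjusted test keeps its error rate. The argument is about precision and consistency only.

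Last, the outcome window in {20a} opens at week 14 and so overlaps T0. If T0 is among the responses, adding it as a covariate would use it twice. This is right, and the fix must deal with it. T0 also follows allocation in the schedule, although it precedes the first session.

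**Conclusion.** The point holds in a limited form. The article names the baseline score for the linear mixed models and gives the logistic mixed model no baseline term, although the score is collected and the trial is sized on proportions. Only the binary between-arm comparisons are affected.

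The direction of the gain is secure if the T0 score is prognostic. Its size is not known: roughly 2 to 14 points for latent correlations of 0.3 to 0.7, and about 5 to 8 at 0.5. These figures assume 34% against 70%, 29 per arm, one visit and no dropout, and so only approximate the repeated-measures model. Visits run to 8 to 10 months postpartum, and one correlation need not hold for all of them. This is a worthwhile improvement to the wording, not a flaw in the primary analysis.

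**What to change.** Add to {20a}, in words such as: *The logistic mixed models will also contain the T0 score of the same scale, as a continuous fixed effect. Only visits T1 to T5 enter the response. For each binary outcome an adjusted risk difference will be given beside the conditional odds ratio.*

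Limiting the response to T1 to T5 removes the overlap with the window that opens at week 14. The risk difference is needed because an odds ratio conditional on baseline is not comparable with an unadjusted one.

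The cost is a few lines of text and one further parameter per model. No new data, visits or participants are required. The analysis plan should carry the same wording.

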#### Interim analyses {21b}

There will be no planned interim analysis that would require any adjustment of the significance level (critical value).

#### Methods for additional analyses (e.g., subgroup analyses) {20b}

In subgroup and regression analyses, effects of age, gestational age, and level of education will be explored.

#### Methods in analysis to handle protocol non-adherence and any statistical methods to handle missing data {20c}

All participants will be analyzed in the group they were randomized to following the intention-to-treat principle. Early study discontinuation will be treated as an independent right censoring in the primary analysis. In case of substantial or differential study discontinuations, the validity of the independent censoring assumption will be explored in shared random-effects models of the primary endpoint and time to study discontinuation. Multiple imputation models will be applied in case of missing data. For the knowledge questionnaires, we will follow questionnaire-specific guidance to impute missing data. All details of the statistical analyses, including definitions of analysis populations, will be prespecified in the statistical analysis plan.

#### Plans to give access to the full protocol, participant level-data, and statistical code {31c}

Information will be provided on request.

### Oversight and monitoring

#### Composition of the coordinating center and trial steering committee {5d}

The Institutional Review Board (IRB) or Independent Ethics Committee (IEC) is a body whose primary purpose is to safeguard the rights, safety, and well-being of human subjects involved in research activities conducted under its authority. The HMC Institutional Review Board will be responsible for overseeing monitoring, which is delegated to Clinical Research Monitor(s) (CRM). The HMC IRB office will appoint the CRM. CRM(s) are responsible for site initiation visits and monitoring visits. Monitoring is arranged in line with the IRB study-related risk assessment. The monitor(s) will be familiar with the study protocol and all study procedures before conducting the visits. Initial site training, routine, and close-out monitoring will be planned and conducted throughout the life span of the study. The first monitoring visit will occur after 20 first subjects are enrolled. Consecutive visits will occur at the end of the study. The study will be conducted in full conformance with principles of the “Declaration of Helsinki,” Good Clinical Practice, and within the laws and regulations of the Ministry of Public Health in Qatar, respecting autonomy, justice, and informed consent and fast track ethical approval under protocol number (MRC-05-087) and electronic registration (MRC-01-20-1129). Accepting or rejecting to participate will not affect the usual patient care.

#### Composition of the data monitoring committee, its role and reporting structure {21a}

There will be a formal external independent monitoring by MRC ethical committee. The monitoring includes site visits to the study setting to review informed consents and perform remote checks of Cerner’s database and documentations.

#### Adverse event reporting and harms {22}

The mitigation plan total score showed to be 24, indicating low risk, and the risk assessment showed that the benefits outweigh the risk. According to corporate policies and guidelines, women who will show suicidal thoughts will get an urgent referral to be assessed by mental health services staff.

#### Frequency and plans for auditing trial conduct {23}

The first monitoring visit will occur after 20 first subjects are enrolled. Consecutive visits will occur at the end of the study. During the monitoring visits, the monitor(s) will review 50% of data collection sheets and 50% telephone scripts. After each monitoring visit, the CRM will debrief the study team, i.e., comment on them for things done right and highlight areas that need improvement. At the close-out visit, the monitor(s) will ensure that all queries are resolved, the study product is accounted for and returned or destroyed, and study documents are properly archived.

#### Plans for communicating important protocol amendments to relevant parties (e.g., trial participants, ethical committees) {25}

Approval for protocol modifications and amendments will be sought from the ethical committees at HMC. All changes will be noted in the study registration.

#### Dissemination plans {31a}

This study protocol and study results will be published in major journals to disseminate the study results. Authorship will be shared between persons involved in the study following the International Committee of Medical Journal Editors (ICMJE). Professional writers and persons not directly involved in the writing will not be granted authorship.

## Discussion

To our knowledge, this study is the first research to examine the effectiveness of maternal low-intensity psychosocial telemental interventions in preventing perinatal distress in response to COVID-19 in Qatar.

Cumulative evidence showed that individual psychosocial interventions were more effective than group interventions in preventing and treating perinatal depression. Specifically, face-to-face CBT revealed a protective effect (OR 0.64; 95% CI [0.53–0.75]) and a preventive effect (OR 0.39; 95% CI [0.17–0.60], p 0.001) [26]. Therefore, the regional body of research agreed on the beneficial effects of face-to-face psychosocial interventions. However, there is a lack of studies concerning the effect size of the telemental health approach on perinatal mental health an identified gap to be tested.

The results from this study will show whether maternal low-intensity psychosocial telemental interventions is preventive or not and whether it is recommended to be part of the antenatal package delivered to pregnant women during the COVID-19 pandemic.

One of this study’s strengths is at the level of methodology; applying randomization as a strategy could deal with bias and determine the effectiveness of an intervention in a reliable approach [27]. The prospective nature of the design ensures the temporality between variables and preserves the causation effect. Utilizing a probability sampling technique preserves the external validity of the study. Furthermore, several strategies were employed to decrease the measurement bias, which included extensive training, blinding, and selecting reliable screening tools for assessment. Moreover, it will provide valuable insights into the acceptability of telemental interventions among pregnant women in Qatar, but it is not without limitations. The sample size is not big enough, limiting the generalization of results, and loss of follow-up could be a challenge.

## Trial status

Not recruiting yet. Protocol version: October 20, 2020. It is estimated to start recruiting in June 2021, and recruitment will be completed in June 2021.

## Data Availability

Access to the final trial dataset will be limited to the authors and sponsor of the study.

## Abbreviations

WHO: World Health Organization
COVID-19: Coronavirus disease 2019
USPSTF: United States Preventive Services Task Force
SARS-CoV-2: Coronavirus severe acute respiratory syndrome coronavirus 2
MRC: Medical Research Centre
RCTs: Randomized controlled trials
WWRC: Women Wellness and Research Centre
VSee: Virtual Single Execution Environment
EPDS: Edinburgh Postnatal Depression Scale
SPSS: Statistical Package for Social Sciences
CBT: Cognitive behavioral therapy
mhGAP: Mental Health Gap Action Programme
CRM: Clinical Research Monitor
ICMJE: International Committee of Medical Journal Editors
OR: Odds ratio
CI: Confidence interval
